### 2.8. Study Follow-Up and Outcome Assessments

The durations of follow-up and treatment are equal at 2 years. In our study, all participants will be evaluated 8 times: at baseline and in weeks 2, 4, 8, 26, 52, 78, and 104. After the qualified participants sign the informed consent form, they will document the characteristics of their own symptoms in the baseline case report form (CRF) and then record the baseline (first visit) physical and laboratory examination data. In weeks 2 and 4, participants will complete the Spleen Qi Deficiency Symptoms Grading and Quantifying Scale (SQD scale) and a physical examination. In weeks 8, 26, 52, 78, and 104, an ECG and laboratory examination, including routine blood, urine, and stool tests, are required. Gastrin-17 and* Helicobacter pylori* will be assessed at both weeks 52 and 104. Gastroscopy will be performed at only baseline and the last visit.  Table 2 provides an overview of the study procedures.

### 2.9. Sample Size Estimation

This RCT is a superiority study. From an overall consideration, we will restrict the type I error (*α*) and type II error (*β*) to 0.05 and 0.2, respectively. The variation between groups and the combined standard deviation of the primary outcome were estimated at 6.0 and 13.0, respectively, based on the results of a preliminary observational study. In addition, a maximum rate of 20% withdrawal or loss to follow-up was adopted. Therefore, with the corresponding sample size estimation equation [18] and the consideration of funding constraints, we computed an expected sample size of 200, with 100 in each group.

### 2.10. Statistical Analysis

We will conduct an interim analysis at week 52 and a final analysis at week 104 with the help of the statistical software SPSS v23.0.

Specifically, an intention-to-treat analysis will be adopted for primary outcomes, while the per-protocol analysis will be performed as a sensitivity analysis. The last observation carried forward method will be used for missing data due to loss to follow-up. Continuous and categorical variables will be analyzed by t-test (or analysis of variance) and Pearson chi-squared test, respectively. In addition, continuous variables with a skewed distribution will be compared with the nonparametric rank-sum test. A P value ≤ 0.05 will indicate statistical significance for all the comparisons mentioned above, and group sequential method will be used to adjust the significant boundary for multiple t-test [19]. Subgroup analysis stratified by type of NOGDs (nonatrophic gastritis versus functional gastrointestinal disorders) and infection of* Helicobacter pylori* (yes versus no) will be performed. Furthermore, an analysis based on safety data set with no imputation will also be conducted. The incidence of AEs in the two groups will be compared using the Pearson chi-squared test, and all the AEs will be described in detail.

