### 2.7. Outcomes

#### 2.7.1. Primary Outcome

The primary outcome is the change in the score of the Spleen Qi Deficiency Symptoms Grading and Quantifying Scale (SQD scale), which was derived from a classic scale in the Clinical Guidelines of New Drugs for Traditional Chinese Medicine to Validate Spleen Qi Deficiency Symptoms [13]. The SQD scale consists of 17 items that assess (1) stomach distension, (2) abdominal distension, (3) physical fatigue and weakness, (4) mental fatigue and taciturnity, (5) loss of appetite, (6) abnormal stools, (7) stomach pain, (8) stomach tightness, (9) abdominal pain, (10) acid reflux, (11) belching, (12) nausea and vomiting, (13) abnormal bowel sounds, (14) powerless defecation, (15) sallow complexion, (16) loss of taste and hypodipsia, and (17) facial and limb edema. Items 1-6 focus on primary symptoms, and the other items focus on secondary symptoms. The scale assesses all the symptoms of SQD, including the duration of each episode (0-3 points, available for items 1-2 and 7-9), the severity (0-3 points, not available for item 13), and the number of episodes per day (0-4 points, except 0-3 for item 5) and per week (0-5 points). The score of each item will be used to calculate the total score, with 2 points for primary symptoms and 1 point for secondary symptoms. As a result, the total score ranges from 0 to 292, and higher scores indicate more severe symptoms. Compared with the original scale, we have added four symptoms (items 1, 7, 10, and 11) and defined 5 primary symptoms. In addition, we assess not only the severity, which is included in the former scale, but also the duration and the number of episodes per day and per week for these symptoms. For more details, see Table S1 in the supplementary material.

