### 2.13. Discontinuation and Withdrawal

After the assessment of previous compliance, study of the corresponding participant will be discontinued for the following reasons, and the participant will be withdrawn without laboratory examination.The symptoms of SQD worsen and the patient must be treated with an alternative regimen to improve his/her statusThe SAEs occurred. All SAEs will be reported by our principle investigators to the ethics committee of the local hospital and the Jiangxi Food and Drug Administration Agency within 24 hours. Several emergency measures will be taken to minimize the harm to patients when a SAE occurred. We will immediately assign senior doctors to implement rescue measures according to the corresponding guidelines. If acute toxicity caused by overdose is determined, the doctors will give measures to accelerate the drug excretion, and, if necessary, the intensive care (e.g., electrocardiograph monitoring and assisted respiration) will be performed until patients' vital signs are stable. If the patient is unable to come to the research hospital, we will advise him/her to visit the local hospital and give consultation with the local doctors, and, if necessary, we will appoint senior doctors to the local hospitalThe patient decides to take prohibited drugs to improve NOGDsPoor compliance includes an intake dose less than 80% of that required or two follow-ups beyond the specific deviation rangeParticipant has personal concerns

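### Per-protocol is the sensitivity analysis named for the primary result, but it is probably selected in part on the outcome and leaves the last-observation-carried-forward assumption untested

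*Protocol article*

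**What the plan says.** All references are to the protocol article.

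- **Outcome (2.7.1).** "The primary outcome is the change in the score of the Spleen Qi Deficiency Symptoms Grading and Quantifying Scale".
- **Primary analysis (2.10).** "an intention-to-treat analysis will be adopted for primary outcomes".
- **Missing data (2.10).** "The last observation carried forward method will be used for missing data due to loss to follow-up".
- **Sensitivity analysis (2.10).** "the per-protocol analysis will be performed as a sensitivity analysis". No other is named for the SQD score.
- **No-imputation analysis (2.10).** "an analysis based on safety data set with no imputation will also be conducted". This concerns the safety set and stands next to the comparison of adverse events, so it is not a second check on the SQD score.
- **Withdrawal (2.13).** One reason is that "symptoms of SQD worsen and the patient must be treated with an alternative regimen". Others are a severe adverse event, a decision to take prohibited drugs for the gastrointestinal disorder, poor compliance and personal concerns. On intake, poor "compliance includes an intake dose less than 80% of that required". When a reason applies, "the participant will be withdrawn without laboratory examination".
- **Attrition.** Section 2.9 allows for up to 20% withdrawal or loss. Section 3 lists attrition bias from loss to follow-up among the limitations.

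**The concern.** The doubtful step in the primary analysis is what to assume about participants who leave before week 104. LOCF supplies one answer. A useful sensitivity analysis keeps everyone who was randomised and changes that answer.

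Per-protocol instead changes the population. One withdrawal reason is worsening of the symptoms that the primary outcome scores, and another (prohibited drugs for the disorder) is plausibly linked to them. If these participants are left out, membership of the set depends on something that happens after randomisation and is tied to the outcome.

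At stake is how the result will be read. If ITT and per-protocol agree, that does not show the result survives other assumptions about those who left. If they disagree, the cause could be selection, adherence or imputation, and the comparison cannot separate them. The attrition bias that section 3 expects would remain unexamined by the check that section 2.10 names.

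**Working it through.** **The plan's own figure.** Section 2.9 gives a difference of 6.0, SD 13.0, α 0.05, β 0.2, 20% loss and 200 participants. Two-sided, n per arm = 2 × (1.960 + 0.842)² × 13² / 6² = 73.7, so 74. Then 74 / 0.8 = 92.5, so 93 per arm and 186 in total. The stated 200 is somewhat larger and is not in dispute. Only the 6.0 and the 13.0 are used below.

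**Step 1: what each analysis does with a participant who leaves.**

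| | ITT with LOCF | Per-protocol |
|---|---|---|
| Participant lost to follow-up | kept, last score used | probably left out |
| Withdrawn for worsening or prohibited drugs | kept, presumably by LOCF (2.10 words the rule for loss to follow-up only) | probably left out |
| Assumption about unseen scores | last score persists | not varied; the participant is removed |

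**Step 2: how far selection could move the estimate.** Let the change score be normal with SD 13, lower being better. If everyone above a cut-off c leaves, the mean of those who remain is

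E[X | X < c] = μ − 13 × φ(z)/Φ(z), with z = (c − μ)/13.

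The documents give neither the share withdrawn for worsening nor a cut-off, so both are assumptions. Take placebo mean 0 and HGMX mean −6, and choose c to give an average withdrawal of 5%, 10% or 20%:

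| Average withdrawn | c | Placebo / HGMX withdrawn | Means of those remaining | Per-protocol difference |
|---|---|---|---|---|
| 5% | 18.9 | 7.3% / 2.7% | −1.94, −6.85 | 4.91 |
| 10% | 14.1 | 13.9% / 6.1% | −3.35, −7.67 | 4.33 |
| 20% | 8.2 | 26.3% / 13.7% | −5.78, −9.31 | 3.54 |

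The last row spends the whole 20% allowance on this one reason, so it is an extreme.

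**Step 3: softer selection.** Withdrawal happens before week 104 and need not follow the final score closely. In a simulation where the tendency to withdraw correlates only partly with the final score, the per-protocol difference is:

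| Correlation | 10% withdrawn | 20% withdrawn |
|---|---|---|
| 0.3 | 5.84 | 5.80 |
| 0.5 | 5.59 | 5.38 |
| 0.8 | 4.91 | 4.41 |

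Across steps 2 and 3 the range is about 3.5 to 5.8 against a true 6.0.

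**Step 4: no true effect.** Both arms have mean 0. When a share w with the worst scores leaves, the mean of the rest is −13 × φ(z)/(1 − w), with z the upper-w normal point:

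- w = 5%: −1.41
- w = 10%: −2.53
- w = 15%: −3.57
- w = 20%: −4.55

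With equal withdrawal the per-protocol difference is 0. With 15% against 5% it is 3.57 − 1.41 ≈ 2.15 from unrounded means. With 20% against 10% it is 4.55 − 2.53 ≈ 2.01. Either way it favours the arm that lost more worsened participants.

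**The case against.** Several points against this are sound.

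- **The article is a condensed source.** A reader might infer that the trial has no other sensitivity analysis. That cannot be established, because an unseen analysis plan may name more. What stands is that section 2.10 itself gives per-protocol this role, and it suits the role poorly.
- **The per-protocol set is undefined.** Section 2.13 governs withdrawal from the study, not membership of an analysis set. A compliant participant withdrawn under the rule could be kept with the last score carried forward. Exclusion is the likelier reading, since such a participant has not completed the planned course, but it is an inference. If they were kept by LOCF, the LOCF assumption would again go untested.
- **The rule is narrow.** A reader might infer that everyone who worsens is removed. The text requires both worsening and the need for an alternative regimen.
- **The size depends on invented inputs.** With a cut-off of +5 points, the difference falls to 3.78 (37% below 6.0) at a placebo mean change of −5, and to 4.44 (26% below) at −10. But 5 points is under 2% of a scale that runs from 0 to 292. At a placebo mean of −10, cut-offs of 10, 15 and 20 give 5.0, 5.5 and 5.75, a loss of 16%, 9% and 4%. No single shrinkage figure can be defended.
- **A harmful product would not be hidden in this model.** A reader might infer that it could look neutral. With a placebo mean of −5, a product mean of +1 and a cut-off of +5, the means of those remaining are −9.95 and −6.97, so a 6-point harm still shows as about 3.0. It is attenuated, not erased.
- **ITT remains primary**, and section 3 discloses attrition bias. This limits the consequence to how robustness is judged.

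**Conclusion.** The point holds as a poorly chosen stated method. The named check probably drops leavers whose departure is related to the outcome, and in any case it does not vary the LOCF assumption. It therefore says little about whether the ITT result is robust to missing data.

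Its numerical effect is uncertain. Under the illustrative assumptions above, a true difference of 6.0 appears as about 3.5 to 5.8. A null effect stays null with equal withdrawal, or becomes about 2 points in either direction when withdrawal for worsening differs by 10 percentage points. These figures rest on a normal change score with SD 13, assumed withdrawal shares and the exclusion of withdrawn participants from the per-protocol set.

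It would go too far to say that per-protocol is uninformative for every purpose, or that the bias runs in a known direction. It can still be reported as supportive evidence on those who followed the protocol, and the primary ITT analysis is not displaced.

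**What to change.** In section 2.10:

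1. Label the per-protocol analysis as supplementary, and define its set if the full protocol does not already do so.
2. Name as the sensitivity analysis a delta-adjusted (tipping-point) multiple imputation of the SQD score on the full randomised set. Worsen the imputed scores of HGMX participants who left in steps, over a range that the sponsor justifies in advance, and report the delta at which the conclusion changes.

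If an existing analysis plan already contains such an analysis, section 2.10 should point to it in place of per-protocol.

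The cost is a short text change and one extra analysis of data already planned, with no change to visits, sample size or participant care. The downside is that a positive result may prove less robust than a per-protocol comparison would have suggested.

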The main purpose of this RCT is to clarify the long-term efficacy, safety, and compliance of HGMX, as a dietary TCM formula, in patients with SQD and NOGDs, with the guidance of TCM theory and evidence-based medicine methodology. The randomization of this RCT is standardly designed to minimize the selection bias and the period of follow-up is enough to observe the long-term efficacy and safety. Before the beginning of the trial, we appointed a training group contained senior methodologists, pharmacists, and physicians to conduct a standard operation procedure training in each research hospital. The diagnosis of TCM syndrome and the measurement of patient-reported outcomes will be performed by well-trained TCM physicians according to the standards to increase the consistency between difference investigators and hospitals. We also prespecified two sets of subgroup analysis based on expert's opinion and biological mechanism and used the group sequential method in repeated measures to reduce the probability of type I error. The results of the trial will be reported in strict accordance with the checklist of Consolidated Standards of Reporting Trials (CONSORT) Extension for Chinese Herbal Medicine Formulas. Therefore, this RCT can be expected to produce high-quality evidence.

This study may have some limitations. First, we will use an adjusted scale to assess SQD symptoms without reliability and validity tests, which could introduce a detection bias. We will conduct reliability and validity tests based on our study outcome data to test whether there exist any defects in reliability and validity. Second, because the placebo consists of early rice and oats and will be undertaken regularly according the study protocol, the patients in the placebo group may correct some bad diet habits during the participation, which may have positive effects on NOGDs and lead to bias in results (i.e., the estimate may tend to be conservative). Third, although we will take various measures to improve the patient compliance, the loss to follow-up is still probably inevitable during the long-term follow-up, resulting in attrition bias.

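### Carrying the last SQD score forward over 104 weeks can bias the week-104 difference in either direction and counts carried values as observed

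*Protocol article*

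**What the plan says.** Section 2.10 of the protocol article sets the analysis of the primary outcome, the change in SQD score: "an intention-to-treat analysis will be adopted for primary outcomes, while the per-protocol analysis will be performed as a sensitivity analysis". The next sentence gives the only missing-data method that the article names: "The last observation carried forward method will be used for missing data due to loss to follow-up". The test follows: "Continuous and categorical variables will be analyzed by t-test (or analysis of variance) and Pearson chi-squared test, respectively", with a rank-sum test for skewed variables. The no-imputation analysis mentioned later in that section concerns the safety data set. The final analysis is at week 104.

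Section 2.8 sets the visits: "all participants will be evaluated 8 times: at baseline and in weeks 2, 4, 8, 26, 52, 78, and 104". Section 2.9 plans for attrition: "a maximum rate of 20% withdrawal or loss to follow-up was adopted". Section 2.13 lists reasons for withdrawal, among them worsening SQD symptoms that need another regimen, serious events, prohibited drugs and poor compliance. The Discussion concedes that "the loss to follow-up is still probably inevitable during the long-term follow-up, resulting in attrition bias".

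**The concern.** LOCF takes the last recorded score as the week-104 score. This is right on average only if symptoms would not have changed after drop-out, or if the later changes cancel between arms. Three features of this trial make that hard to rely on.

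- **Age of the carried value.** Visits are dense early (weeks 2, 4, 8) and sparse later. A week-2 score carried to week 104 is 102 weeks old, and the stated interest is long-term efficacy.
- **Missingness linked to outcome.** Worsening SQD symptoms are a ground for withdrawal. If the worsening falls between visits up to 26 weeks apart, the carried score can be the better one recorded before it.
- **Possible imbalance between arms.** Section 2.6 says that the placebo differs slightly in taste and smell, and withdrawals for adverse events or poor compliance may also differ by arm.

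At stake is the primary efficacy estimate. Part of the planned 6.0-point difference could be created or hidden by who leaves and when. The t-test would also treat carried scores as if they had been measured at week 104.

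**Working it through.** **Inputs from the document.** Difference 6.0, SD 13.0, alpha 0.05 (sidedness not stated; two-sided assumed), power 80%, maximum 20% withdrawal or loss, 100 per arm (section 2.9); visit weeks (section 2.8).

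**Inputs assumed, not in the document.** Placebo improvement by week 104: C = 0 to 20 points. Share of the week-104 change reached by drop-outs when last seen: f = 25% to 75%. Loss by arm, HGMX/placebo: 20%/20%, 10%/30% and 30%/10%. All lost participants are carried forward.

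**The plan's own figure.** n per arm = 2 × (1.96 + 0.84)² × 13² / 6² = 73.7, so 74. Dividing by 0.8 gives 93 per arm, 186 in total; a t-based calculation gives 75 and 94, 188 in total. The stated 200 is a little larger. It is not reproduced exactly, but there is no shortfall.

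**Standard error and power.** SE = 13 × √(2/n).

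- 100 per arm treated as observed: SE = 1.84, power for 6.0 = 90.4%.
- 80 per arm observed: SE = 2.06, power for 6.0 = 83.1% (82.7% by t-test).
- Ratio = √0.8 = 0.894, so the nominal SE is 10.6% below the one that the observed week-104 values support.

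**Expected LOCF difference.** With loss d_T in the HGMX arm and d_P in the placebo arm, mean improvement is (C + 6)(1 − d_T(1 − f)) under HGMX and C(1 − d_P(1 − f)) under placebo. The difference is

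6 − (1 − f)[d_T(C + 6) − d_P·C].

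| Loss HGMX/placebo | Bracket | Range over C and f |
|---|---|---|
| 20%/20% | 1.2, for any C | 5.1 to 5.7 |
| 10%/30% | 0.6 − 0.2C | 5.55 (C = 0, f = 25%) to 8.55 (C = 20, f = 25%) |
| 30%/10% | 1.8 + 0.2C | 1.65 (C = 20, f = 25%) to 5.55 (C = 0, f = 75%) |

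**Type I error with no true effect.** The spurious difference is C(1 − f)(d_P − d_T), compared with SE 1.84.

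- Equal loss: 0 points, so 5%.
- 10%/30%, C = 10, f = 75%: 0.5 points, 5.9%.
- 10%/30%, C = 20, f = 25%: 3.0 points, 37%.

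**Simulation check.** 4,000 trials per scenario, seven post-baseline visits, adjacent-visit correlation 0.7, common improvement 15, drop-out after weeks 8 to 78. Mean LOCF estimates against a true 6.0 were 5.53 (20%/20%), 7.03 (10%/30%) and 3.99 (30%/10%). With no true effect, type I error was 5.4% with equal loss and 10.9% with 10%/30%. In the equal-loss null scenario the nominal SE (1.89) matched the actual spread of the LOCF estimator (1.91).

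**The case against.** The strongest reply is that the harm is conditional. The document gives no symptom trajectory and no drop-out pattern by arm, so neither the direction nor the size of bias can be derived from it. With equal loss LOCF does modest damage: the difference shrinks to 5.1 to 5.7, type I error stays at 5%, and power at 100 per arm is 79% to 87%, close to the 83% from 80 observed per arm. The 10%/30% scenarios average 20%, but exceed the planned maximum if that is meant per arm. All of this stands.

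A reader might infer more than the document supports:

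- **That LOCF will bias the result, or favour HGMX.** The calculation shows movement either way, and towards zero with equal loss.
- **That the full 20% will be carried forward.** That figure combines withdrawal and loss, while the LOCF sentence names only loss to follow-up. How data missing after section 2.13 withdrawals are handled is not stated.
- **That power falls from 90%.** The protocol claims 80%; 90% arises only if all 100 per arm are observed.
- **That the standard error is wrong in every sense.** It is too small relative to the observed week-104 information, but in the simulation it described the LOCF estimator correctly. The error inflation came mainly from bias.
- **That gastroscopy and gastrin-17 will be set to zero change.** The article says "Gastroscopy will be performed at only baseline and the last visit", so carrying forward could use only the baseline. But the LOCF sentence directly follows one about primary outcomes, and its scope is unclear.
- **That no sensitivity analysis beyond per-protocol exists.** The article names only that one, and it does not test the LOCF assumption, but a fuller plan may list others.

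None of this makes LOCF a sound primary method here. The article fixes it, so the choice is not a detail left for later.

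**Conclusion.** The concern holds as a risk to the primary estimate. LOCF can bias the week-104 SQD difference in either direction, and the plan gives no ground for assuming that it is conservative. Taking week 104 as the target (the final analysis) and a true difference of 6.0, the assumed scenarios give expected estimates from 1.65 to 8.55. They stay within 5.1 to 5.7 if loss is 20% in both arms. Type I error is 5% with equal loss and about 6% to 37% with 10%/30% loss and a common improvement of 10 to 20 points. The nominal standard error is 1.84 where about 80 observed values per arm support 2.06. Only the SD, planned difference, sample size, visit schedule and 20% maximum come from the document; trajectories and the split of losses are assumptions. Section 2.13 strengthens the point, because it makes missingness depend on the outcome being measured.

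**What to change.** 1. Make the primary analysis a mixed model for repeated measures on all scheduled SQD scores, with treatment, visit, treatment-by-visit and baseline score, and the week-104 contrast as the estimate. Say what becomes of the rank-sum provision for this outcome.
2. Add one delta-adjusted or reference-based multiple-imputation sensitivity analysis. The mixed model assumes that missingness is explained by observed scores, and withdrawal for worsening after the last visit would break that assumption.
3. Keep LOCF at most as a supplementary table.
4. State that the missing-data rule also covers data missing after section 2.13 withdrawals.
5. State whether the rule covers gastroscopy and gastrin-17. If it does, do not carry the baseline forward, since that imputes zero change.

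The change should be made before unblinding. It costs wording and a little programming: seven post-baseline SQD scores per participant are already scheduled, and SPSS has a mixed-model procedure. The price is slightly wider intervals. About 80 observed per arm give about 83% power for 6.0 before group-sequential adjustment, so replacing LOCF needs no extra patients. The article does not give the sequential boundary; at a final level of 0.0294, for example, 80 per arm would give 77%. That shortfall would come from the boundary, not from replacing LOCF.

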### 2.2. Sites and Participant Recruitment

The potential participants will be recruited in three ways: oral promotion by researchers, hospital posters, and web page publicity. Patients with NOGDs will be recruited from five tertiary hospitals: First Affiliated Hospital of Nanchang University, Second Affiliated Hospital of Nanchang University, Jiangxi Hospital of Traditional Chinese Medicine, Nanchang Hospital of Integrated Traditional Chinese and Western Medicine, and Nanchang Hongdu Hospital of Traditional Chinese Medicine. Subjects who meet the inclusion criteria will be required to sign the informed consent form to show an overall understanding of study details prior to study participation.

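### The primary test on change in SQD score is valid, but it forgoes precision from the baseline score, and the skewness switch leaves the primary effect measure unfixed

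*Protocol article*

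**What the plan says.** Section 2.7.1 makes the change in total SQD score, on a range of 0 to 292, the primary outcome. Table 2 schedules the scale at baseline and at all seven later visits.

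Section 2.10 covers all continuous variables in one rule: "Continuous and categorical variables will be analyzed by t-test (or analysis of variance) and Pearson chi-squared test, respectively". It then adds that "continuous variables with a skewed distribution will be compared with the nonparametric rank-sum test". No covariate is named, no criterion for skewness is given, and the primary outcome is not exempted from the switch. Analyses are planned at weeks 52 and 104, and "group sequential method will be used to adjust the significant boundary for multiple t-test". The primary analysis is by intention to treat, with last observation carried forward (LOCF) for participants lost to follow-up.

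Section 2.9 sizes the trial on a difference in means: "The variation between groups and the combined standard deviation of the primary outcome were estimated at 6.0 and 13.0, respectively".

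**The concern.** There are two separate weaknesses in what the article fixes.

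**Baseline is subtracted, not modelled.** A change score gives baseline a fixed weight of 1. Change is usually correlated with baseline, so a group that starts higher by chance tends to fall further. The change-score comparison carries that through to the estimate. A model with baseline as a covariate estimates the weight from the data, corrects for the imbalance and has smaller residual variance. The data are already being collected.

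**The primary test depends on the data.** A t-test addresses a mean difference, which is the quantity behind the 6.0-point sample size. A rank-sum test addresses whether values in one arm tend to exceed those in the other. Which of these is the primary result depends on an undefined judgement of skewness. Skew is plausible for a symptom score bounded at 0. The sequential boundary mentions only the t-test, so its use with a rank-sum result, or with different tests at the two looks, is not settled.

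**Working it through.** **Inputs from section 2.9:** difference 6.0, SD 13.0, α 0.05, β 0.2, 20% loss, 100 per group. A two-sided test is assumed, because sidedness is not stated.

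**The plan's own figure.** n per arm = 2 × [13 × (1.960 + 0.842) / 6]² = 73.7, so 74. Dividing by 0.8 gives 92.5, so 93 per arm and 186 in total, against 200 stated. The stated number is on the safe side, and the section says funding was also considered. The gap does not bear on this point.

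**Gain from baseline adjustment.** Let s be the SD of the score, equal at baseline and follow-up (assumed), and r the baseline-to-week-104 correlation (assumed).

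- Variance of change = 2(1 − r)s²
- Residual variance with baseline as covariate = (1 − r²)s²
- Ratio = (1 + r)/2

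If 13.0 is the SD of change, the effective SD is 13 × √[(1 + r)/2]. Power is from the two-sample t-test. The column for 80 per arm is completers after 20% loss. The column for 100 per arm is everyone analysed under intention to treat with LOCF, and it assumes that carried-forward values have the same effect and SD.

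| r | Variance cut | Effective SD | n per arm for 80% power | Power, 80 per arm | Power, 100 per arm |
|---|---|---|---|---|---|
| unadjusted | – | 13.00 | 74 | 82.7% | 90.1% |
| 0.3 | 35% | 10.48 | 48 | 94.9% | 98.1% |
| 0.5 | 25% | 11.26 | 56 | 91.8% | 96.3% |
| 0.7 | 15% | 11.99 | 63 | 88.2% | 94.1% |
| 0.8 | 10% | 12.33 | 67 | 86.4% | 92.8% |

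The n column uses the normal approximation, as in the reproduction above.

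**If 13.0 is instead the SD of the score**, a reading section 2.9 does not exclude, the SD of change is 13 × √[2(1 − r)]. At r = 0.3 that is 15.38, and power with 80 per arm is 69% for the change score against 86% with adjustment. At r = 0.7 it is 10.07, and power is 96% against 98%.

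**Chance imbalance, as an illustration.** A baseline difference D shifts the expected difference in change by −(1 − r)D. At r = 0.5 an SD of change of 13 implies a score SD of 13. With 100 per arm, an imbalance of 1.96 standard errors is 1.96 × 13 × √(2/100) = 3.6 points. The shift is 0.5 × 3.6 = 1.8 points, or 30% of the 6.0 target. This is a fairly extreme draw, not the expected case.

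**Type I error of the switch.** Simulation used 6,000 trials per scenario, 80 per arm, nominal 5%, with an assumed rule: Shapiro-Wilk on the residuals, then a t-test or rank-sum test.

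| Distribution | Fixed rule, then one test | Either test significant |
|---|---|---|
| Normal | 5.3% | 6.1% |
| Gamma | 4.9% | 6.8% |
| Lognormal | 5.1% | 7.5% |

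The simulation standard error near 5% is √(0.05 × 0.95 / 6,000) = 0.3 points. A single rule fixed beforehand holds the level. Inflation appears only when whichever test succeeds is reported.

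**The case against.** **Validity.** A two-sample t-test on change is unbiased over randomisation and controls type I error, and it matches the basis of the sample size. A reader might infer that the plan discards the baseline score or yields a biased estimate. It does neither. The change score uses baseline with a fixed weight, and chance imbalance causes error only conditional on the imbalance observed. This objection stands: the cost is precision.

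**Size.** Without adjustment, power already exceeds the planned 80% if 13.0 is the SD of change: 83% with 80 per arm and 90% with 100. The correlation and the equal variances are assumptions, and at r = 0.8 the gain is only about 3 to 4 points. This also stands, and it is why a range is given.

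**Type I error.** A reader might infer that a data-dependent test inflates it. The simulation does not support that for a fixed rule, and the article does not propose running both tests and choosing. What remains is that no criterion is stated, so the text does not exclude such a choice.

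**Power of the rank test.** With a pure 6-point shift and skewed data, the same simulation gave the rank-sum test more power than the t-test: 93.2% against 83.0% (gamma) and 99.8% against 82.6% (lognormal). That is a fair reason to report it. It does not make it an estimate of the 6.0-point mean difference.

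**Centre and other covariates.** A reader might infer that hospital, disorder type and *Helicobacter pylori* status must enter the model. Section 2.5 states no stratification, so omitting them contradicts no design feature. The article gives no between-centre variance or prognostic effect from which to compute a gain.

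**Condensation.** An article may leave model detail to a fuller document. Here, however, the tests are stated outright, and the stated choice can be judged. The reference to analysis of variance does not change this, since no factor or covariate is named with it.

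**Conclusion.** The point holds as one of efficiency and pre-specification, not validity. The stated primary comparison is sound but gives up 10% to 35% of the variance for r between 0.8 and 0.3. This rests on 13.0 being the SD of change and on equal variances at baseline and follow-up. In power, the gain is roughly 4 to 12 points with 80 per arm and 3 to 8 points with 100.

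Separately, the skewness switch leaves the primary effect measure open, and the sequential boundary is not stated for the rank-sum alternative. No material inflation of type I error is shown unless the test is selected after results are known.

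**What to change.** Name one primary analysis: a linear model for the SQD score (or its change) at week 104 with treatment and baseline SQD score as terms. With baseline in the model, the treatment estimate is the same for score and change. Report the adjusted mean difference with its 95% confidence interval whatever the distribution looks like, and state that the group sequential boundary applies to this model's treatment test. Name the rank-based comparison as a sensitivity analysis. Adding centre, disorder type and baseline *Helicobacter pylori* status as covariates is optional; if they are wanted, fix them before unblinding.

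The cost is a change of wording in the analysis section. No new data or visits are needed, and SPSS, the software named in section 2.10, fits this model.
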